## Abstract

**Background:**

Early diagnosis of dementia benefits both patient and caregiver. Nevertheless, dementia in primary care is currently under-diagnosed. Some educational interventions developed to improve dementia diagnosis and management were successful in increasing the number of dementia diagnoses and in changing attitudes and knowledge of health care staff. However, none of these interventions focussed on collaboration between GPs and nurses in dementia care. We developed an EASYcare-based Dementia Training Program (DTP) aimed at stimulating collaboration in dementia primary care. We expect this program to increase the number of cognitive assessments and dementia diagnoses and to improve attitudes and knowledge of GPs and nurses.

**Methods:**

The DTP is a complex educational intervention that consists of two workshops, a coaching program, access to an internet forum, and a Computerized Clinical Decision Support System on dementia diagnostics. One hundred duos of GPs and nurses will be recruited, from which 2/3 will be allocated to the intervention group and 1/3 to the control group. The effects of implementation of the DTP will be studied in a cluster-randomised controlled trial. Primary outcomes will be the number of cognitive assessments and dementia diagnoses in a period of 9 months following workshop participation. Secondary outcomes are measured on GP and nurse level: adherence to national guidelines for dementia, attitude, confidence and knowledge regarding dementia diagnosis and management; on patient level: number of emergency calls, visits and consultations and patient satisfaction; and on caregiver level: informal caregiver burden and satisfaction. Data will be collected from GPs' electronic medical records, self-registration forms and questionnaires. Statistical analysis will be performed using the MANOVA-method. Also, exploratory analyses will be performed, in order to gain insight into barriers and facilitators for implementation and the possible causal relations between the rate of success of the intervention components and the outcomes.

**Discussion:**

We developed multifaceted dementia training programme. Novelties in this programme are the training in fixed collaborative duos and the inclusion of an individual coaching program. The intervention is designed according to international guidelines and educational standards. Exploratory analysis will reveal its successful elements. Selection bias and contamination may be threats to the reliability of future results of this trial. Nevertheless, the results of this trial may provide useful information for policy makers and developers of continuing medical education.

**Trial registration:**

ClinicalTrials.gov ID NCT00459784

## Background

### Diagnosing dementia in primary care

Dementia is an increasing challenge for health care and social systems in developed countries. In Europe, 6.4% of the elderly over 65 years suffer from dementia, with an increase from 0.8% in the group aged 65–69 years to 28.5% at age 90 years and older. The total number of dementia patients in Europe is expected to increase from 7 million in 2000 to over 16 million in 2050 [1]. Currently, dementia seems to be under-diagnosed [2-4]. More than 50% of dementia patients living in the community have not been diagnosed by a GP or specialist [5,6]. In the Netherlands, detection of dementia takes place around one year before admission to a nursing home and three years before death [7], which is rather late.

Early diagnostic evaluation of patients possibly suffering from dementia is beneficial for both patient and caregiver. Reversible causes of dementia will be identified and treated timely. Formal disclosure of dementia diagnosis allows patients and carers to make future plans and provides early access to support services [8]. These actions may prevent or decrease psychological distress in patients [9]. Early education and support for caregivers facilitates adjustment over a longer period of time; it prevents crisis situations and delays nursing home admissions [10,11]. Non-pharmacological interventions, such as psychosocial interventions (10;11) and occupational therapy [12], have been shown to play a key role in dementia management. Pharmacological treatment may primarily be beneficial when started in the early stages of dementia. However, drugs that are currently available have only moderate effect on cognitive symptoms and ADL [13]. In the near future, disease-modifying drugs might become available since they are already subject to phase two and three trials.

Despite the acknowledged benefits of early diagnosis of dementia, both patients and doctors are reluctant to initiate cognitive assessment. Patient-related delay in early recognition of dementia is often caused by lack of insight into their condition, their view of memory loss symptoms as being normal for their age and fear of the negative consequences of dementia diagnosis [4]. GPs report that their own lack of knowledge and skills in diagnosing and treating dementia prevents them from starting diagnostic work-up in the early stages of dementia [14]. Other GP-related barriers include the absence of clear diagnostic guidelines and reliable, user-friendly screening tools, lack of time, of financial reward, of adequate resources such as access to neuropsychological consultations and neuro-imaging investigations, and lack of prescription right for cholinesterase inhibitors [15]. Thus, many GPs are sceptical about the benefits of early diagnosis, because they feel they have little to offer dementia patients and their caregivers [14,16,17]. Moreover, disclosure of diagnosis is considered to be difficult, because it may negatively influence patient-doctor relationships and take away patients' and caregivers' hopes [18,19]. GPs also fear the risk of diagnostic errors. Evidence of under-recognition of dementia has also been shown in primary care nurses for similar reasons [20]. Also, collaboration between primary care nurses and GPs is not very well developed, although dementia diagnosis and management may profit from it. This lack of collaboration is caused by conflicting expectations, domain discussions and poor coordination of care [21].

### Developing a Dementia Training Program (DTP) for primary care providers

To improve early detection in primary care, guidelines on dementia diagnosis and management were developed in several countries [22-25]. A multifaceted implementation program in Denmark did not show effects on adherence to practice guidelines [26]. Research teams in the UK and USA also developed educational programmes for implementation of their national guidelines. These programmes were successful in raising the rate of early dementia diagnosis and improving professionals' knowledge [27,28]. However, they showed only minor improvement in attitudes of health care providers regarding dementia diagnosis and regarding management of dementia in primary care [29,30]. Implementation strategies in these programs included the use of small group sessions, a Computerized Clinical Decision Support system (CDSS) [27], and internet support [28,29].

The educational programs in the studies discussed above primarily focused on GPs. However, dementia care management performed by collaborative interdisciplinary teams was found to be more effective in improving the quality of care than that performed either by GPs or primary care nurses [31]. Therefore, we designed a Dementia Training Program (DTP) for collaborative duos of GPs and primary care nurses, focused on teaching them how to share tasks in early diagnosis and management of dementia. Another unique component of our DTP is individual coaching, which has shown promising results in modifying behaviour of health professionals [32]. Furthermore, our Dementia Training Program is a multifaceted program [33] and consists, in addition to individual coaching, of two small-group interactive workshops [34,35] and a Computerized Clinical Decision Support System.

### Objectives

The objective of this paper is to describe the design of a randomised controlled intervention study, aimed at determining the effectiveness of a multifaceted Dementia Training Program (DTP) for general practitioners and primary care nurses, based on current national guidelines. We expect the DTP to improve professional performance in dementia diagnostics and disease management and GPs' and nurses' attitudes and knowledge regarding dementia.

## Methods

### Study design and setting

This study is an outcome assessor-blinded randomised controlled trial. A cluster-randomised design will be used to compare duos of GPs and nurses (Figure 1).

**Figure 1 F1:**
[figure not shown]
Procedure of recruitment and randomization.

### Study population

We plan to recruit 100 duos of GPs and practice or district nurses in the province of Gelderland, the Netherlands. We will approach all general practitioners in this province by mail and ask them to participate in the study. Participating GPs may choose to cooperate with their own practice nurse or with a district nurse. All GPs and affiliated nurses within the county are eligible for this study.

Frail elderly people, suspected of suffering from cognitive problems are the target group to be diagnosed and treated according to Dutch dementia guidelines. [22,25]. From this target group additional data on satisfaction and informal carer burden will be obtained. Informed consent will be obtained from patients and from their legal representatives. The Local Medical Ethical Committee, Commissie Mensgebonden Onderzoek Regio Arnhem – Nijmegen, concluded that this study did not include experiments with patients and therefore did not need to be tested for approval.

### Bias control and randomisation

Randomisation will take place after measurement of baseline data. Duos of GPs and nurses will be randomly allocated to one of the two conditions: 1. Dementia Training Program (DTP) and 2. no training at all; control group. (Figure 1). Randomization will be concealed; a person who is not responsible for recruiting subjects and has no knowledge of the study conduct will perform it on a computer.

Cluster-randomisation will be performed in order to avoid contamination by the effects of possible exchange of information within a cluster. A cluster was defined as all GPs working in the same practice or as all GPs working together with the same nurse.

In order to assure an equal distribution of baseline characteristics, duos will be randomised with adaptive weights regarding cluster size (one vs. more than one GP), age, sex, high or low percentage of elderly patients in practice (< or > 15%), practice location (rural or urban area) and nurse affiliation (district or practice).

Adherence to guidelines will be assessed by two independent researchers. In order to exclude the possibility of detection bias, these researchers will be blinded to the outcome of randomization.

### Intervention: Dementia Training Program (DTP)

DTP consists of two workshops and an individual coaching programme, including case-based consultation either by phone or by e-mail. Participants have access to an internet forum for discussion with colleagues, additional literature and individual training on dementia diagnosis and management. A Computerised Clinical Decision Support System on dementia diagnostics and management will be available to support GPs in decision making in daily practice. The content of the DTP and the CDSS is based on the recently published, evidence-based Dementia Guideline for Primary Care [36]. The DTP is graphically presented in Figure 2[37].

**Figure 2 F2:**
[figure not shown]
**Graphical depiction of the interventions of this trial on improving primary dementia care**. **a)** Dutch Dementia Guidelines for general practitioners and for community nurses. **b)** Workshop on dementia diagnosis and management for GPs and nurses as a duo. **c) **Coaching of GPs and nurses on dementia diagnostics and management in daily practice according to national guidelines and using the EASYcare assessment. **d)****e)** Usual dementia care performed by GPs without coaching. **f)** Availability internet forum for patient questionnaires (MMSE, GDS, EASYcare assessment), discussion with colleagues, additional literature. **g)** Availability Computerised Clinical Decision Support System on dementia diagnosis.

Methods used in the DTP to stimulate collaboration between GPs and nurses are the following:

1. Training of collaborative performance of geriatric function assessment according to dementia guidelines, using the EASYcare assessment. This assessment of geriatric function is carried out by a nurse and interpreted by a GP. Therefore, it requires collaboration in order to be performed.

2. Collaboration and training in fixed duos.

3. Training in collaborative workout of a dementia case assignment.

4. Presentation and discussion of 'task sharing' between GPs and nurses in dementia diagnostics and management.

5. Availability of a Dementia Guideline for Primary Care, which has exclusively been written for this project, based on evidence-based Dutch guidelines [22,25] and recent studies investigating the diagnosis and management of dementia in primary care. This Dementia Guideline for Primary Care contains a flow chart and recommendations regarding 'task sharing' and consultation moments between GPs and nurses.

#### Workshops

Two workshops were developed according to approved educational standards [38]. The first workshop was designed for both GPs and nurses to train collaboration in diagnosis and management of dementia. During the second workshop, nurses and GPs will be educated separately. The second workshop for GPs focuses on dementia diagnostics and pharmacological options, while the second workshop for nurses concentrates on dementia care issues.

#### Case-based coaching program

After attending to the workshops, GPs and nurses will select eligible patients in their own practices during the following 9 months. GPs and nurses will be coached in their performance of these patients' assessments. Three geriatric nurses will coach the participating nurses; a trained GP specialized in geriatrics will coach the participating GPs. Coaching will be performed by telephone. The coaching program is divided into two phases; in phase 1 the participants will be intensively supervised, whereas phase 2 is demand led. To gain insight into the exact content of the coaching program, coaches will keep diaries of their own performances.

#### Phase 1

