### Outcome measures and data collection

Primary outcome measures are the numbers of cognitive assessments and dementia diagnoses over a period of nine months, which will be measured at baseline (T0) and nine months later, at the end of the study (T1). Secondary outcomes are GPs' and nurses' attitude, confidence and knowledge regarding dementia diagnosis and management, which will be measured at baseline (T0) and nine months later, at the end of the study (T1). Other secondary outcomes are the rate of adherence to national guidelines for dementia diagnosis and management, patient satisfaction, informal carer burden and satisfaction, number of emergency calls, visits and consultations. Baseline demographic characteristics collected from GPs and nurses are: age, sex, practice experience, practice size, percentage of elderly people > 65 years and the availability of chronic disease management programs in practice. Baseline demographic characteristics collected from patients and their informal caregivers are: age, sex and co-morbidity (Table 1).

**Table 1 T1:** Outcome measures

**Variable**	**Primary outcomes**	**Secondary outcomes**	**Background**	**Instrument/Source**	**T_0_**	**T_1_**	**T_x_**

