**Informal carers**							
Age	□	□		Own questionnaire		□	□
Sex	□	□		Own questionnaire		□	□
Satisfaction intervention	□		□	Own questionnaire	□	□	
Burden informal caregiver	□		□	SSCQ^3^	□	□	

T_0 _is baseline measurement

T_1 _is follow up measurement, after 9 months

T_x _is 3 months after starting each assessment

^1 ^measurement of 'number' during a period of 9 months

^2 ^Electronic Medical Dossier

^3 ^Short Sense of Competence Questionnaire

Data on adherence to national guidelines, the number of emergency situations and the number of cognitive assessments and dementia diagnoses will be retrieved from GPs' Electronic Medical Records (EMD), from interviews with GPs and nurses and from self registration forms [41]. Self-made questionnaires will provide information on baseline characteristics, on data on GPs' and nurses' attitudes, competencies and knowledge regarding dementia diagnosis and management and on patient and informal carer satisfaction. Burden of informal carers will be assessed using the Short Sense of Competence Questionnaire (SSCQ) [42]. Data on duos' performance during the 'coaching phase' will be included in the analysis.

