## Discussion

In this paper we described the study design of a randomized controlled trial that evaluates the effects of a Dementia Training Program (DTP) for duos of GPs and primary care nurses. A novelty in this program is the training in fixed collaborative duos. We chose focus on collaboration, because dementia care management in collaborative interdisciplinary teams was found to be effective in improving the quality of care [31]. Another novelty in our approach is the inclusion of an individual coaching program in the DTP. This educational method appears to be highly effective modifying professional behaviour [32]. Whereas some studies used single interventions [27], we developed multifaceted intervention, since multifaceted interventions are usually more effective [33]. For the design and evaluation of the DTP, we used the MRC framework [44]. The exact content of the DTP will be described in more detail in a separate article. Methodologically strong elements in this study are the following. We avoid selection bias by computerized randomization and minimisation. Two independent blinded outcome assessors will contribute to overcoming detection bias. In addition to a confirmatory analysis, we will perform an exploratory analysis. In this way, we can clarify how certain intervention components influence the rate of success and through which pathways.

Below, we describe the design characteristics that may interfere with the reliability and validity of the future results. Firstly, the method of participant recruitment may threat the external validity of the study: GPs and nurses are free to decide whether they want to participate. This may mean that this group of participants is more interested in dementia care than their average colleagues. Therefore, they may be more motivated to learn and perform better than their non-participating colleagues would do after receiving the same training. In addition, they may already be taking better care of dementia patients and their caregivers than their non-participating colleagues. However, the possible effects of this bias would run counter to our hypotheses by negatively affecting the chances to detect differences between the experimental and the control group. These effects might affect the probability of making a type II error (incorrectly accepting H-0) but they cannot cause the making of a type I error (incorrectly rejecting H-0).

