Secondly, we cannot exclude the possibility of contamination arising by chance contacts and possible knowledge exchange between GPs and nurses from different allocation conditions. We try to overcome this problem by cluster randomization: GPs from the same practices and GPs working with the same nurses are allocated to the same group.

Finally, performance bias can occur. GPs and nurses are fully aware of their assignment to either the experimental or the control group. We try to overcome this problem by reminding participants in the control group every two months of their involvement in the study.

In spite of these elements of bias, the results of this trial may provide useful information for policy makers and developers of continuing medical education. The intervention is designed according to recently reported MRC guidelines and educational standards; exploratory analysis will reveal its successful elements. In the study design, bias is avoided if possible and still its setting is one of every day practice. Dissemination of the results of this study is planned for 2009.

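### Satisfaction, carer burden and adherence rest on patients identified after allocation, so randomising duos does not protect these secondary comparisons from selection bias

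*Protocol article*

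**What the plan says.** The relevant statements are spread over several sections of the protocol article.

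- **Unit and timing of allocation** (Bias control and randomisation): duos are allocated in clusters. "Randomisation will take place after measurement of baseline data". The minimisation factors describe the duo and the practice, not individual patients with suspected dementia.
- **What one arm is taught** (Developing a Dementia Training Program): the programme is "focused on teaching them how to share tasks in early diagnosis and management of dementia".
- **How patients enter** (Case-based coaching program): once the workshops are over, "GPs and nurses will select eligible patients in their own practices during the following 9 months".
- **Blinding of those who select** (Discussion): "GPs and nurses are fully aware of their assignment to either the experimental or the control group".
- **Source of the patient and carer data** (Study population): the target group is frail elderly people suspected of cognitive problems. "From this target group additional data on satisfaction and informal carer burden will be obtained".
- **Outcomes concerned** (Outcome measures and data collection): the secondary outcomes include "the rate of adherence to national guidelines for dementia diagnosis and management, patient satisfaction, informal carer burden and satisfaction". The notes to Table 1 define a time point T_x, which "is 3 months after starting each assessment".
- **The claim** (Discussion, among the strengths): "We avoid selection bias by computerized randomization and minimisation".

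The limitations in the Discussion are volunteering by GPs and nurses, contamination and performance bias. Volunteering is said to be able to cause a type II error but not a type I error. The abstract, by contrast, lists selection bias as a possible threat.

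**The concern.** Randomisation makes the duos comparable. It does not make comparable the people whom the duos later decide to assess. A patient contributes satisfaction data, a carer contributes a burden score, and a case can be scored for guideline adherence only once someone has suspected a cognitive problem and acted on it. In the intervention arm that decision is taken after allocation, by people who know their allocation and whom the programme is meant to make quicker to act.

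A difference in carer burden or satisfaction between arms could then reflect which patients were found rather than how they were cared for. The better the programme does on its primary outcome, the more room there is for the two patient groups to differ. A reader who relies on the statement that selection bias is avoided would take such a difference as a randomised effect.

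**Working it through.** **1. The plan's own figure.** The inputs come from Sample size calculations: 50% versus 65%, control to intervention 1:2, two-sided 0.05, power 0.80, 5 patients per cluster, ICC 0.05.

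- Pooled proportion: (0.50 + 2 × 0.65)/3 = 0.60.
- Control patients: [1.96 × √(1.5 × 0.60 × 0.40) + 0.8416 × √(0.50 × 0.50 + 0.65 × 0.35/2)]² / 0.15² = [1.176 + 0.508]² / 0.0225 ≈ 126.
- Intervention patients: 2 × 126 = 252, so 378 in total.
- Design effect: 1 + (5 − 1) × 0.05 = 1.2, and 378 × 1.2 = 453.6.
- GPs: 453.6/5 = 90.7, rounded up to the stated 91.

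The figure reproduces and is not disputed here. Its use is to show that the plan treats 50% and 65% as the proportions in the two arms.

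**2. Difference in case finding at the planned effect.** Of every 100 people with dementia, control duos would find 50 and intervention duos 65. If everyone whom a control duo would find would also be found by an intervention duo, the extra 15 have no counterpart in the control arm: 15/65 = 0.15/0.65 = 23%. A smaller effect than planned lowers this share, and less overlap between the two sets raises it. The share refers to dementia cases. Satisfaction and burden come from the wider group with suspected cognitive problems, so it does not carry over directly to that sample.

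**3. Order of events.** Baseline data are collected, duos are randomised, the intervention arm attends workshops, and its duos then select patients over 9 months. T_x is counted from the start of each assessment, so it exists only for people whom a duo chose to assess. I have not relied on the tick marks in Table 1, which were not legible in the text available to me.

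**4. Which outcomes this reaches.**

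| Outcome | Measured on | Set fixed before allocation? |
|---|---|---|
| Numbers of cognitive assessments and dementia diagnoses | Duo | Yes |
| Duos' knowledge, attitude, confidence | Duo | Yes |
| Patient satisfaction | Patients identified | No for intervention duos; inferred for control duos |
| Carer burden and satisfaction | Carers of those patients | As above |
| Guideline adherence | Listed under GPs and nurses, but can be scored only on patients who entered work-up | As above |

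For the primary counts, finding more people is the intended effect and is measured on the randomised units. For the last three rows, the set being compared depends on a step that the intervention is meant to change.

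**The case against.** Four points can be made on the other side.

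- **The selection sentence describes one arm only.** It belongs to the coaching programme, which control duos do not receive during the trial. This stands. The article does not say how control patients and carers are identified, and a condensed article may leave that out. Identification after allocation is inferred for control duos from the description of the target group and from T_x. If the procedures do differ between arms, comparability is worse, not better.
- **The statement on selection bias credits computerised randomisation and minimisation, which act on duos.** In that sense it is right, and the abstract does concede a possible threat. But the statement is not limited to duos, and the only selection problem the Discussion develops is volunteering by professionals.
- **Adherence is scored by two blinded researchers.** This guards against biased scoring. It does not change which patients are available to be scored.
- **The outcomes are already secondary, and analysis detail may sit in an analysis plan.** Both are true, and they limit the weight of the point. No analysis plan, however, can make patients identified after allocation a randomised group.

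A reader might also infer that emergency contacts are affected because the abstract calls them a patient-level outcome. The article does not support this: Table 1 lists them under GPs and nurses as a number over 9 months, and nothing says they are counted only over selected patients.

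**Conclusion.** The concern holds for patient satisfaction, carer burden and satisfaction, and guideline adherence. Between-arm comparisons of these outcomes are not protected by randomisation, and the Discussion's statement that selection bias is avoided is true only of the allocation of duos. The mechanism follows from stated design features for the intervention arm and by inference for the control arm.

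The only size that the protocol's figures give is 23% of intervention-arm dementia cases. It rests on the planned effect being reached and on control cases being a subset of intervention cases.

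Two stronger readings are tempting. The first is that the trial as a whole is biased. It is not on this ground, because the primary counts and the duo-level measures are taken on the randomised units. The second is that the bias must favour the programme by a known amount, because the extra patients would be milder cases with less burdened carers. The article speaks of early diagnosis but gives no severity or burden figures for such patients, so neither direction nor size can be fixed from it.

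**What to change.** 1. Limit the Discussion statement on selection bias to the allocation of duos.
2. Add differential identification of patients after randomisation to the limitations. Say that, unlike the volunteer bias described there, it could produce a type I error.
3. Report satisfaction, carer burden and adherence as non-randomised and exploratory. Show the patient and carer characteristics already collected (age, sex, co-morbidity) by arm.
4. Use adjustment for age, sex and co-morbidity only as a sensitivity analysis. None of these measures dementia stage, so adjustment cannot be presented as removing the bias.

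I would not ask GPs to list suspected patients before randomisation. In control practices such a list is itself a prompt to look for cases, and it could shrink the contrast on the primary outcomes.

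The cost is wording and a by-arm table from data already planned. The downside is weaker claims for these secondary outcomes.
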